#### Treatment effects on sleep parameters

To analyze changes in sleep patterns over time and between treatment conditions, multilevel mixed-effects models will also be utilized. Sleep outcomes include the following outcomes from both sleep diaries and actigraphy: sleep duration, sleep onset latency, wake after sleep onset, midsleep timing, sleep onset, and sleep offset. Additionally, sleep quality will be calculated from sleep diary and sleep fragmentation from actigraphy. The fixed effects structure will encompass time (*days since treatment start*), and the interaction between time and treatment condition (*Light@Home*,* LightCafé*, and* LightCafé* +), allowing us to explore how sleep patterns evolve throughout the intervention and whether these changes differ across conditions. The inclusion of random intercepts for participants and study centers, along with random slopes for time within participants, will be evaluated based on model fit criteria. Additionally, the model will incorporate a factor indicating whether a day is a weekend or weekday to account for social jet lag experienced by participants.

Furthermore, we will investigate the relationship between subjective sleep measures from sleep diaries and objective data obtained from actigraphy through correlation analyses. Next, we will assess the total PSQI and ISI scores over time and between conditions using a linear mixed model approach as described above, focusing on the timepoints of *Baseline, 4 weeks post-treatment, 10 weeks post-treatment*, and *4 months post-treatment* instead of *days since treatment start.*

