### Intervention description {11a}

In all study arms, participants are subjected to BLT in adherence to Dutch BLT guidelines [72], utilizing an Innolux LED light Lamp delivering light with an illuminance of 10,000 lx at a distance of 70 cm and a color temperature of 3800 K. BLT sessions, lasting 30 min each, are scheduled from Monday to Friday between 7:30 AM and 10:30 AM.

The number of BLT sessions is contingent upon the individual response of each participant, with a maximum duration of 3 weeks. Initially, participants undergo five consecutive BLT sessions during the workweek. Subsequently, the therapeutic efficacy is evaluated utilizing the QIDS-SR during the Friday session. If the QIDS-SR falls below 6, remission is inferred, leading to the termination of BLT. Alternatively, an additional five sessions are administered. This evaluation and decision process is repeated at the end of the second week. If the QIDS-SR score is still above 6, a third and final week of treatment is provided.

This individualized strategy is intended to reduce the small risk of (hypo)manic switches, which occur in less than 2% of bipolar patients and almost exclusively in those not maintained on mood stabilizers [11, 73]. We will continuously monitor for (hypo)manic symptoms using the Young Mania Rating Scale (YMRS; [74]) and clinical observation: a YMRS score ≥ 13 and clinician‐identified symptoms will lead to immediate treatment cessation, while scores of 10–11 will prompt a joint review with a second clinician to decide on discontinuation [75, 76].

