### Treatment phase

During the treatment phase, participants receive 1, 2, or 3 weeks of BLT within their assigned condition. Every Friday, depressive symptoms are assessed using the QIDS-SR, regardless of whether the participant received treatment that week. Treatment will be continued as long as QIDS-SR-score is higher than 6, with a maximum of 3 weeks. Treatment tolerability and mania symptoms are assessed using the YMRS after each week of BLT. EMA, actigraphy, and light logger usage continue throughout the treatment.

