### Follow-up phase

After the treatment has been completed, EMA, actigraphy, and light logger usage are extended for an additional week and are discontinued on the Sunday at the end of this additional week. The post-treatment DLMO assessment (M3) and MRI scan (MRI-2) also occur within this first week after BLT.

Following these assessments, a post-treatment evaluation (PT1) is scheduled 4 weeks after the start of treatment, which includes a series of online questionnaires and an online MADRS assessment. During this meeting, participants receive general insights into their EMA data. The online follow-up questionnaires (F1) are sent 10 weeks after the start of treatment, with the second set of follow-up questionnaires (F2) distributed 4 months after the start of treatment, after which study participation is discontinued.

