### Secondary Study Outcomes

#### Subjective Assessment of Depressive Symptoms, Relapse Rates and Functional Outcomes

Multilevel mixed-effects models will be constructed to assess depressive symptom improvement, measured weekly during therapy and at follow-up assessments using the QIDS-SR scores as the dependent variable. Fixed effects will include timepoint as an categorical variable (baseline, 1 week, 2 weeks, 3 weeks, 4 weeks, 10 weeks, and 4 months), and the interaction between timepoint and treatment condition (*Light@Home*,* LightCafé*, and *LightCafé* +). Random intercepts and slopes will be included for participants and study centers, as well as random slopes for time within participants, based on model fit criteria. Confounding variables (age, sex, clinical diagnosis, and credibility/expectancy of treatment) will also be evaluated and included as necessary. A variable will be added to account for treatment duration (1 week, 2 weeks, 3 weeks). Similar models will be considered for analyses of relapse rates, functional outcome, and Quality of Life with inclusion of the respective timepoints as fixed effects (see Table 1).

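### The sleep models use days since treatment start, most naturally a straight line, while recording is shorter in earlier remitters; a shared but curved sleep change can then appear as an arm difference

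*Protocol article*

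**What the plan says.** The section on treatment effects on sleep parameters specifies the model for the daily diary and actigraphy outcomes: "The fixed effects structure will encompass time (*days since treatment start*), and the interaction between time and treatment condition". It adds that "random slopes for time within participants, will be evaluated based on model fit criteria", together with a weekend/weekday factor. It names no week factor, no curvature, no on/off-treatment term and no arm main effect, and it does not say whether pre-treatment days enter.

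The number of recorded days depends on response. Under Intervention description {11a}, "The number of BLT sessions is contingent upon the individual response of each participant, with a maximum duration of 3 weeks", and "If the QIDS-SR falls below 6, remission is inferred, leading to the termination of BLT". Under Follow-up phase, "After the treatment has been completed, EMA, actigraphy, and light logger usage are extended for an additional week". The Actigraphy section confirms a window of baseline week, treatment and one further week.

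The QIDS-SR model is handled differently. There, "Fixed effects will include timepoint as an categorical variable", and a term for treatment duration is added. The sleep section itself uses discrete timepoints for the PSQI and ISI in place of days.

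**The concern.** The day-by-condition interaction is the planned test of whether sleep changes differ between strategies. A straight line describes every patient's course by one slope. If the true course bends, the best-fitting slope depends on how many days are recorded. Here the number of days is decided by remission, which the trial itself compares between arms in its time-to-remission analysis. An arm that remits faster contributes more short series, so its fitted slope can differ from the others although sleep responded identically.

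A bend is plausible. A flat baseline week followed by any change is already one. The background section expects relief within 1 to 2 weeks. In LightCafé+, the aim changes to not shifting sleep once current sleep onset is within 30 minutes of target, which implies a plateau.

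At stake is the interpretation of a secondary between-arm comparison. The primary MADRS analysis is unaffected.

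**Working it through.** **No figure to reproduce.** The article gives no effect size, variance or power for the sleep models.

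**Inputs from the article.** Seven baseline days, 1-3 treatment weeks and one further week give 21, 28 or 35 days. With day 0 as the first session, the last recorded day is 13, 20 or 27. N = 231, taken as 77 per arm; the diary runs through EMA in 120 participants. Alpha is 0.05, and the interaction test has 2 df.

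**Step 1: slope against series length.** For a step of size D after the first k of n equally spaced days, the least-squares slope is D × 6k(n−k) / [n(n²−1)]. With k = 7 and, for illustration, D = 30 minutes:

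- n = 21: 30 × 588/9,240 = 1.91 min/day
- n = 28: 30 × 882/21,924 = 1.21 min/day
- n = 35: 30 × 1,176/42,840 = 0.82 min/day

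The same sleep change gives more than a twofold difference in slope (1.91/0.82 = 2.3).

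**Step 2: when this reaches the arm contrast.** The expected mixed-model estimate was computed with the same true sleep course in every arm. Rejection rates came from the noncentral chi-square. Assumed: residual SD 1, intercept SD 0.8, random-slope SD 0 or 0.03 per day, baseline days included.

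- Equal remission speed: spurious interaction 0 for every shape.
- Shared change straight over the whole window: spurious interaction 0 and rejection 5.0%, even with strongly different remission speed.
- Shared plateau (5-day time constant), week-1 remission 10/25/40%: the slope in the fastest-remitting arm is 12.7% (random intercept) or 17.4% (random slope) larger than in Light@Home.

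Rejection in the last case:

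| Shared change (residual SD) | 0.4 | 0.8 | 1.2 | 2.0 |
|---|---|---|---|---|
| Random intercept | 7.8% | 17.0% | 33.8% | 76.2% |
| Random slope | 6.6% | 11.8% | 21.4% | 52.2% |

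- Same plateau, week-1 remission 20/27/35%: slope 6.1% to 8.4% larger, rejection 5.4% to 24.1%.
- Flat baseline, then linear: bias of opposite sign (−1.8% to −5.3%), rejection 5.0% to 8.9%.

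Adding an arm main effect changes these results hardly at all.

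**Step 3: on a minutes scale.** Assumed: 30-minute shared shift reached early and then flat, within-person SD 45, between-person SD 60. The expected-value calculation gives about 8-9% for week-1 remission of 20/30/40% and 11-15% for 15/30/45% with baseline days, and 6-8% without them. A separate simulation of 300 trials per scenario (Monte Carlo SE 1.3 to 2.3 points) gave about 10% and 20% with baseline days. The upper end is therefore not firm. In the diary subsample the bias is unchanged, but the noncentrality is 120/231 = 0.52 of that for all participants, so rejection is lower.

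**Step 4: sensitivity to a real step.** For a true 0/10/20-minute step difference with equal treatment durations, power is about 91% for the line with a random slope and baseline days, against 99% for a step or week model. If baseline days are left out, the line has about 6% power. With no arm main effect, a constant level difference from day 0 produces almost no slope.

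**Step 5: weekly categories.** With time as week by arm, rejection is 5.0% in every scenario of Step 2. This assumes that remission is unrelated to the sleep path.

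**The case against.** **Linearity is inferred.** The article never says linear or continuous, calls its plan an initial framework, and an SAP may fix the functional form. This stands as a caution. But the article does name the time variable and the interaction to be tested, and a day count with random slopes is hard to read otherwise, especially beside the explicitly categorical QIDS-SR model.

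**Baseline days may not enter.** This also stands. Without them a pure step gives slope 0 at every series length, and the inflation is small. That reading carries the power problem of Step 4 instead.

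**The inputs are generous.** The 30 minutes and 45-minute SD match the DLMO power inputs in the saliva-sampling section and are not sleep figures. The graded effects in the sample-size section (−0.25, −0.33, −0.4) span only 0.15, and a remission gap of that order leaves rejection at about 5%. A common timing shift is also doubtful in LightCafé+, where sleep may be advanced, held or delayed by patient. All of this limits the size, not the mechanism.

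**Stronger readings.** A reader might infer that any difference in remission speed creates a false sleep effect, or that the faster arm always gains. Step 2 contradicts both: a straight shared change gives none, and a flat-then-linear course reverses the sign. Nor does the article make this interaction the basis of its mechanism claims: the cross-lagged model addresses sleep dynamics, and the mediation analyses concern circadian parameters.

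**Conclusion.** The point holds conditionally. Series length depends on remission, and the stated sleep model has no term that separates length from effect. The artefact requires three things together: time fitted as a straight line, a shared change that is not straight over the recorded days, and arms that differ in speed of remission. Under the assumptions of Step 3, false rejection is roughly 8-15% for week-1 gaps of 20-30 percentage points with baseline days included. It is about 5% for small gaps. The remission gaps, sleep variances and shape of change are not in the article, so these figures show the order of magnitude and do not predict what the trial will find. Separately, the line detects a step-shaped arm difference less well once a random slope is fitted, and hardly at all if baseline days are excluded. This is a worthwhile improvement to a secondary analysis.

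**What to change.** In the section on treatment effects on sleep parameters:

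- Replace days since treatment start with categorical study week (baseline week, weeks 1 to 4 from treatment start), following the QIDS-SR model.
- State that the baseline week is included, and constrain the arms to be equal in it.
- Keep the weekend/weekday factor.
- Make the headline between-arm contrast the change from the baseline week to weeks 1-2, which the schedule records in every participant (days 0 to 13). Report later weeks as supporting.

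Week 2 is off treatment for week-1 remitters, so this contrast compares the strategies as delivered, not sleep under equal light exposure. The write-up should say so.

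Borrowing only the treatment-duration covariate from the QIDS-SR model would not solve the problem: it shifts level and not slope, and it is a post-randomization variable.

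The change needs wording only and no new data. It costs a few more fixed-effect parameters and gives a less compact summary than one slope per arm. The article reports the trial as still enrolling and allows documented, justified changes to the analyses.

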#### Circadian effects of BLT and their relation to the antidepressant outcomes

To analyze changes in circadian parameters, including DLMO, Phase Angle Difference, inter-daily stability, and intra-daily variability, multilevel mixed-effects models will be employed. The fixed effect’s structure will incorporate time (*Baseline vs. Post-treatment*), and the interaction between time and treatment condition (*Light@Home*,* LightCafé*, and *LightCafé* +). Inclusion of random intercepts for participants and study site and random slopes for time within participants will be evaluated based on model fit criteria, including AIC and BIC. Circadian effects will be compared between timepoints by evaluating the fixed effect of time in the model, while the effect of the treatment condition will be interpreted by assessment of the interaction term between time and treatment condition.

Following the assessment of changes in circadian parameters (e.g., DLMO, Phase Angle Difference, inter-daily stability, and intra-daily variability), multilevel mediation analyses will be conducted to determine whether these changes mediate the relationship between timepoint and depressive symptoms (QIDS-SR). Each mediator will be tested individually using an approach based on Bauer et al. [99] which includes decomposing within- and between-person components to yield valid indirect effect estimates in nested data. We will apply bootstrapping (5000 samples) to estimate the indirect path (ab) and construct 95% confidence intervals for each mediator. In addition, moderation analyses will examine whether baseline depression severity or sleep quality interact with treatment conditions to affect depressive outcomes. Results will report direct effects (c′), indirect effects (ab), and any interaction effects (a × b), along with the corresponding confidence intervals and *p*-values.

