### Justification for the saliva sampling sample size

Saliva sampling is optional in the study protocol to reduce participation barriers. The main aim of the saliva sampling is to compare possible shifts in DLMO between conditions. A simulated dataset was created using the *simr* package in R, with a mean DLMO set at 23:00 and extensive between-person variance (*SD* = 120 min) and within-person variance (*SD* = 45 min). Using a mixed-effects model with a random intercept for participants, we simulated a sample of 72 participants measured at two timepoints (pre- and post-treatment). The analysis yielded a power of 96.40% (95% CI 95.05, 97.47) to detect a phase shift of 30 min in DLMO with an alpha level of 0.05. This high power suggests that even with the optional saliva sampling and a sample size of 72 we can confidently assess the effect of BLT on circadian rhythm changes.

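### The overall circadian effect is read from a time term whose meaning depends on unstated contrast coding; the 96.4% power fits only the change over all 72 saliva participants

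*Protocol article*

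**What the plan says.** The section on circadian effects of BLT and their relation to antidepressant outcomes covers DLMO, phase angle difference, inter-daily stability and intra-daily variability. Its mixed models have two fixed-effect components: time (baseline or post-treatment) and the interaction of time with the three conditions. No condition main effect is listed. The section then assigns a role to each component. For the pre-post question, "Circadian effects will be compared between timepoints by evaluating the fixed effect of time in the model"; for the treatment condition, the interaction is read. It gives no contrast coding, reference level or marginal contrast, and names no software for this model.

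The saliva sample size section describes the simulation behind the 72 participants: "Using a mixed-effects model with a random intercept for participants", two timepoints, a between-person SD of 120 min and a within-person SD of 45 min. It mentions no arm term. The result is given as follows: "The analysis yielded a power of 96.40% (95% CI 95.05, 97.47) to detect a phase shift of 30 min in DLMO". The same section names the comparison of DLMO shifts between conditions as the main aim of saliva sampling, but ends by concluding that the effect of BLT on circadian rhythm can be assessed. The section on the choice of comparators makes Light@Home the active control.

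**The concern.** Once time × condition is in the model, the time coefficient has no meaning apart from the coding. Under reference (dummy) coding it is the pre-post change in the reference arm. Under sum-to-zero coding it is the average change over the arms. Reference coding is the default in R, which the article uses for its simulations and for some other analyses, and Light@Home would be the natural reference level. Read that way, the null hypothesis is that DLMO does not shift in Light@Home, whereas the power statement concerns the shift in all 72 participants.

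The contribution of circadian change to the effect of BLT is a secondary objective, and the design expects arms to differ: LightCafé + has its own light timing and blue-light-blocking glasses. The same data could therefore give quite different answers to the pre-post question, depending on a software default that the plan does not fix.

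**Working it through.** **Inputs from the saliva sample size section:** alpha 0.05 (two-sided assumed; sidedness is not stated), shift 30 min, within-person SD 45 min, between-person SD 120 min, 72 participants, two timepoints.

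**Assumption:** 1:1:1 allocation, hence 24 per arm. The ratio is not stated, but balanced blocks of six and stratification by melatonin participation support it.

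**Step 1: reproduce the stated power.** With two timepoints and a random intercept, the between-person variance cancels from the change.
- SD of change = 45 × √2 = 63.6 min.
- SE over all 72 = 63.6 / √72 = 7.50 min; ratio 30 / 7.50 = 4.0.
- Power by noncentral t (71 df) = 97.6%.

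This is close to the stated 96.40%, though just above the upper limit of its simulation interval (97.47%). A one-sided test gives 99.1% and fits worse. The stated figure is therefore the power for the change pooled over 72.

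**Step 2: the time coefficient under reference coding, Light@Home as reference.**
- With a condition main effect: SE = 63.6 / √24 = 13.0 min; power for 30 min = 62.4% (noncentral t, 69 df).
- Without one, with time entered as 0/1 so that the arms share a baseline: ρ = 120² / (120² + 45²) = 14400 / 16425 = 0.877. The variance is 16425(1 − ρ²)/24 + 16425(1 − ρ)²/72 = 158.3 + 3.5 = 161.8. Then SE = 12.7 min and power = 65.5% (normal approximation).
- With 20 to 28 in the arm instead of 24 (condition main effect included): about 56% to 70% (normal approximation).

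**Step 3: compare the two readings.** A mean of 30 with Light@Home at 15 arises from, for example, shifts of 15/37.5/37.5 min.

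| True shifts | Time term, reference coding | Three-arm average (SE 7.50) |
|---|---|---|
| 30 min in every arm | 62–65% | about 98% |
| Light@Home 15, mean 30 | 21–22% | about 98% |
| Light@Home 0, mean 30 | 5% (the alpha level) | about 98% |

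**Step 4: a worked data set.** One simulated data set (72 participants, SDs 120 and 45) had observed changes of −2.5 min in Light@Home, −43.8 in LightCafé and −51.0 in LightCafé +, mean −32.4. The time coefficient was:
- −2.5 (SE 13.5) under reference coding;
- −6.3 (SE 13.2) under reference coding without a condition main effect;
- −32.4 (SE 7.8) under sum-to-zero coding.

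**Step 5: what the interaction test would pick up.** The 2-df test has noncentrality 24 × Σ(shift − mean)² / 63.6², with 63.6² = 4050.
- 0/45/45: 24 × 1350 / 4050 = 8.0; power about 70%.
- 0/30/60: 24 × 1800 / 4050 = 10.7; power about 82%.
- 15/37.5/37.5: 24 × 337.5 / 4050 = 2.0; power about 22%.

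**Step 6: the declared main aim.** For a 30-min difference in shift between two arms of 24, SE = 63.6 × √(2/24) = 18.4 min and power is about 36% (noncentral t, 69 df). The common-baseline model gives about 39%.

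**The case against.** The article does not say that a dummy coefficient will be read. The fixed effect of time, set beside a separately interpreted interaction, is common shorthand for a main effect averaged over arms, and a simulation without arm terms fits that reading. R is named for the power simulations, the cross-lagged model and the variance partitioning, but not for these mixed models. Coding is often left to an analysis plan or the code, and the article presents its statistical section as an initial framework. All of this stands. A reader might infer that the trial will test Light@Home alone; the documents do not support that. What remains is that the article itself selects the term that answers the question, and that term can carry two meanings with very different power.

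A reader might also infer that the trial would miss a circadian effect produced by the café arms. That goes too far as well. The article reads the interaction too, and Step 5 shows that large differences between arms would usually appear there. The protection is weak for moderate differences (about 22% at 15/37.5/37.5).

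Finally, the three-arm average is not obviously the better quantity. LightCafé + aims to advance, delay or hold the clock depending on the participant, and both café arms add lifestyle coaching, so the average mixes different intentions; the Light@Home change is arguably the cleaner estimate of light alone. This also stands. It is a reason to report the arm-specific changes beside the average, not a reason to leave the estimand to a default.

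**Conclusion.** The concern holds as a coding-dependent definition of the overall circadian effect. If Light@Home is the reference level, the named term has about 62–65% power for a common 30-min DLMO shift, and about 21–22% if Light@Home shifts 15 min against a mean of 30. The stated 96.4% describes a different quantity, the change over all 72. Under sum-to-zero coding or a marginal test there is no defect.

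The figures rest on the saliva section's SDs, a two-sided 5% test and about 24 per arm. They apply to DLMO in the optional saliva subsample. The actigraphy parameters share the problem of interpretation but are not limited to the 72. The primary MADRS analysis rests on the interaction and is not affected.

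One mismatch does not depend on coding: the saliva section powers the pooled pre-post shift, while it declares the comparison between conditions as its main aim.

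**What to change.** In the circadian analysis section, replace the reference to the time term by a definition: the overall circadian effect is the model-based pre-post change averaged with equal weight over the three arms, estimated as a linear contrast from the same model. Report each arm's change with its 95% confidence interval beside it.

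In the saliva sample size section, state that the 96.4% refers to this pooled pre-post change and not to the comparison between conditions, for which a 30-min difference between two arms has about 36% power.

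The cost is a few sentences and one contrast statement, with no new data or participants. There is a small downside: the average may be diluted by the mixed timing strategies in LightCafé +. If that arm's mean shift were zero and the others 30 min, the average would be (30 + 30 + 0) / 3 = 20 min, with about 75% power (20 / 7.50 = 2.67). The arm-specific changes are therefore a necessary part of the fix.

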### Personalized chronotherapeutic strategies

In the *LightCafé* + arm, BLT timing is personalized, and participants wear BBG according to their individual sleep–wake rhythms. These adjustments aim to promote sleep regularity and synchronize sleep phase with the endogenous biological night. Before commencing treatment, each participant’s current sleep onset time (CSO) is established based on their baseline sleep data obtained from the Consensus Sleep Diary (CSD; [60]. Following this, a target sleep onset time (TSO) is collaboratively determined through a phone call with a member of the study team. During this conversation, the participant’s daily routine, social and work obligations, and personal preferences for sleep onset and offset are discussed. The aim is to establish a sleep schedule that accommodates approximately 7–8 h of nightly sleep and fits well within the participant’s everyday life.

Based on the relation between CSO and TSO, one of the following timing strategies is employed:*Stabilize*: When CSO is within 30 min of TSO, the aim is to not shift sleep timing and the circadian clock. Morning BLT is administered approximately 11 h after TSO, and participants wear BBG during the last hour before TSO.*Advance*: When CSO occurs more than 30 min later than TSO, the aim is to advance the sleep timing and the biological clock by exposing patients to BLT earlier in the morning (around 8–9 h after CSO) and having them wear BBG during the last 2 h before CSO.*Delay*: In cases where CSO is more than 30 min earlier than TSO, a delay in sleep–wake cycles and the biological clock is the goal. Morning BLT is administered later in the morning (around 11 h after CSO), and BBG are worn in the morning, during the first 2 h after awakening.

The chronobiological strategy is selected and implemented on a weekly basis, based on a reassessment of the CSO, using CSD entries from that week, and the TSO, determined via phone contact. Treatment times will always remain within the 7:30 AM to 10:30 AM window. This time frame was chosen because morning light has been shown to be most effective in reducing depressive symptoms [7]. While some individuals may theoretically benefit from alternative timings, individual adjustments are limited by the practical constraints of the clinical setting. If the prescribed strategy suggests a time outside this window, the closest suitable time within the range is selected.

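### The signed mean DLMO change in LightCafé+ pools patients meant to advance, hold or delay their clock, so the time-by-condition term cannot show whether personalised timing worked

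*Protocol article*

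**What the plan says.** The section on the saliva sampling sample size gives the purpose of the sub-study: "The main aim of the saliva sampling is to compare possible shifts in DLMO between conditions". It simulates 72 participants measured before and after treatment, with a within-person SD of 45 min, and reports 96.40% power for a 30-min shift.

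The section on circadian effects uses mixed models "To analyze changes in circadian parameters, including DLMO, Phase Angle Difference, inter-daily stability, and intra-daily variability". The fixed effects are time and time by condition, and "the effect of the treatment condition will be interpreted by assessment of the interaction term between time and treatment condition". The same circadian changes then enter, one at a time, a mediation analysis of the relation between timepoint and QIDS-SR.

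The section on personalized chronotherapeutic strategies gives LightCafé+ patients one of three goals, depending on how current sleep onset (CSO) compares with target sleep onset (TSO):

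- Stabilize: "the aim is to not shift sleep timing and the circadian clock".
- Advance: "the aim is to advance the sleep timing and the biological clock".
- Delay: "a delay in sleep–wake cycles and the biological clock is the goal".

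The strategy is chosen afresh each week. The article does not say what share of patients is expected in each.

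**The concern.** The intended DLMO change in LightCafé+ is negative, nil or positive depending on the patient. A time-by-condition term for DLMO estimates the difference between arms in mean signed change. For this arm, a mean near zero is what a perfectly working intervention could produce, and also what an intervention that does nothing would produce.

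The other two arms have no personalised timing, and the background section says that morning light reliably advances the clock. Their mean shift may therefore be larger than that of a LightCafé+ arm in which every patient moved as planned.

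Personalised timing of light and darkness is what separates LightCafé+ from LightCafé, and the role of circadian change is part of a stated secondary objective. The saliva sub-study could report a small or misdirected circadian effect of personalisation without having tested whether patients moved towards their targets.

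**Working it through.** **Inputs.** From the saliva sample-size section: 72 participants, two timepoints, within-person SD 45 min, shift 30 min, alpha 0.05 (taken as two-sided). About 24 per arm is an assumption, based on balanced blocks and stratification by melatonin participation. The strategy mix is not in the article and is shown as a range.

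**Step 1: the plan's own figure.** SD of change = 45 × √2 = 63.6 min. SE = 63.6/√72 = 7.5 min. 30/7.5 = 4.0, and power = Φ(4.0 − 1.96) = 97.9%. A paired t calculation gives 97.6%, close to the stated 96.40%. This is the power for one shift in the same direction pooled over all 72. For one arm against another, SE = 63.6 × √(2/24) = 18.4 min, and a 30-min difference has 37% power.

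**Step 2: perfect personalisation.** Let every Advance patient shift by -30 min, every Stabilize patient by 0 and every Delay patient by +30 min.

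- Arm mean = -30 × pA + 30 × pD.
- Extra variance between patients = 900 × (pA + pD) − mean². This is added to 63.6² for LightCafé+.
- Contrast SE = √(SD²/24 + 63.6²/24), where SD is the LightCafé+ SD of change.

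Example, 50/25/25: mean = -15 + 7.5 = -7.5 min; extra variance = 675 − 56.25 = 618.75; SD = 68.3 min; SE ≈ 19.1 min.

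| Advance/Stabilize/Delay, % | LightCafé+ mean, min | Power v an arm with no shift | Contrast v an arm advancing 30 min | Power |
|---|---|---|---|---|
| 100/0/0 | -30 | 37% | 0 | 5% |
| 80/15/5 | -22.5 | 23% | +7.5 | 7% |
| 60/30/10 | -15 | 13% | +15 | 13% |
| 50/25/25 | -7.5 | 7% | +22.5 | 22% |
| 40/30/30 | -3 | 5% | +27 | 29% |
| equal thirds | 0 | 5% | +30 | 35% |

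In every row each patient did exactly what was intended. A positive contrast means that LightCafé+ advanced less than the comparator.

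**Step 3: sensitivity to the size of the shift.** With 45 min in LightCafé+ and 30 min in the comparator, 50/35/15 gives -22.5 + 6.75 = -15.75 min and 60/40/0 gives -27 min, both smaller than the comparator. But 80/15/5 gives -36 + 2.25 = -33.75 min, which is larger. Even the ordering of the arms depends on the unstated mix.

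**Step 4: does another part of the plan supply direction?** The model has no strategy term, aligned change or distance to target. Random slopes leave the mean interaction unchanged and, with two measurements per person, cannot be separated from residual error. The additional analyses cover subgroups by diagnosis and adherence to the prescribed schedule; neither encodes the intended direction.

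**Step 5: mediation.** The mediation concerns timepoint, not arm, and as described is not confined to LightCafé+, so about 72 × 2/3 = 48 participants come from the other arms. If those advance by 30 min, the pooled mean DLMO change is (-30 − 30 − 7.5)/3 = -22.5 min at 50/25/25, or (-30 − 30 + 0)/3 = -20 min at equal thirds. The path from timepoint to DLMO shrinks but does not vanish.

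**Step 6: what alignment recovers.** If the sign is set by the strategy, Advance and Delay patients keep the full 30 min at every mix. Within-arm power is then 64% when all 24 are in Advance, 52% at 50/25/25 (18 patients) and 47% at equal thirds (16 patients).

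**The case against.** The time-by-condition term is a legitimate as-randomised question: does mean DLMO change differ by arm? The article nowhere predicts a larger mean shift in LightCafé+, nor says that a smaller one means failure. DLMO is also not the only circadian measure. Phase angle difference addresses alignment, and inter-daily stability and intra-daily variability carry no advance or delay sign, so they can still show the regularity that the intervention is meant to promote. The strategy mix is unknown; if nearly all patients are in Advance, little is lost. The analysis is secondary, in an optional subsample, and leaves the MADRS comparison untouched. The article calls its plan an initial framework, and a breakdown by strategy could sit in a fuller analysis plan.

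Most of this stands and limits the point. It does not make the signed mean informative about personalisation. The article says affirmatively how the treatment effect will be interpreted, and for DLMO, the measure that the saliva sub-study exists to compare, that reading cannot separate success from no effect. Phase angle does not fill the gap: it can stay constant when sleep and clock move together, which is what Advance and Delay intend.

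A reader might infer that the sub-study is bound to find no circadian effect, or that the mediation paths cancel. The documents support neither. If the comparators advance, the contrast is misdirected rather than null, and the pooled mediation is only diluted.

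**Conclusion.** The point holds for DLMO. The LightCafé+ mean signed change combines opposite intended shifts and cannot show whether the personalised timing worked. With 30-min shifts exactly as intended, the mean lies between -30 min (all Advance) and 0 (equal thirds). Against an arm with no shift, power falls from 37% to 5%; against an arm advancing 30 min, LightCafé+ appears to move the clock less in every mix except all Advance.

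These sizes rest on an assumed mix, a common 30-min shift and about 24 saliva participants per arm. The mechanism follows from the text; how much it matters in this trial is uncertain. The stability and variability measures are unaffected. A reader might also conclude that LightCafé+ must look worse than standard light; Step 3 shows that this depends on inputs the article does not give. This is a modest but worthwhile change to a secondary analysis, held with medium confidence.

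**What to change.** Keep time by condition as the as-randomised description of DLMO change, and specify before analysis:

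1. Within LightCafé+, DLMO change by assigned strategy, and a direction-aligned change with the sign set by the strategy from baseline CSO versus TSO. State which week's strategy counts, since it can change weekly. The data are already collected. This comparison is uncontrolled: regression to the mean in sleep timing could mimic movement towards target, so it should not stand alone.
2. As the randomised comparison, a time-by-arm-by-baseline-sleep-timing term, using continuous actigraphic sleep onset, which is collected in all arms. Label it exploratory.
3. A sensitivity mediation using the aligned DLMO change in LightCafé+.
4. A sentence saying that a smaller signed mean shift in LightCafé+ will not by itself be read as failed personalisation.

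A plain absolute shift is a poor substitute: with an SD of change of 63.6 min, noise alone gives a mean absolute shift of 63.6 × √(2/π) ≈ 51 min.

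The cost is analysis-plan wording, with no new data. The drawbacks are real. With 24 participants, the SE of an arm's mean change is 63.6/√24 = 13 min before any split by strategy. Baseline sleep onset is only a proxy for the CSO-TSO gap in the two arms for which no TSO is described. Adding a target-sleep item at intake would not solve this, because TSO is agreed by phone after randomisation and the article already reports recruitment under way. Chronotype is not a good stand-in either: a late type with a late target would fall under Stabilize.
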